##### Aim 2: Sustainability of AB (Posttest Period to Follow-Up)

The same shared-baseline analyses will be used to determine durability (eg, changes between *after the intervention* and *6-month follow-up*) on the coprimary and secondary outcomes. Specifically, the persistence of a benefit from AB at 6-month follow-up will be estimated from linear contrasts of the postintervention period to 6 months least-square means and analyzed as a noninferiority test of durability. Noninferiority of AB in maintaining benefits relative to control will be declared if the lower 1-sided 95% confidence bound for a given coprimary outcome is less negative than each outcome’s minimum clinically important difference in favor of control.

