### Data Analytic Plan

#### Power Analysis

Our blinded statistician used SAS (version 9.4; SAS Institute) [92] for the power analysis. Our primary outcome requires clinically important improvements in both functional measures (step count and 6-min walk test) and patient-reported outcome (Patient-Reported Outcomes Measurement Information System Physical Function). Allowing for 20% dropouts, 260 participants recruited (130/group; 104/group completing the study) would provide 92.3% power (Cronbach α=.05; 2 sided) to detect the minimum clinically important difference in step count (1000 steps) [93,94] between the AB and HEP groups in the change from baseline to postintervention assessment. This assumes an SD of 2120, which is the upper 80% confidence limit for the SD observed in our pilot study, as recommended [95]. We also assume 50% correlation between preintervention and postintervention measures. This sample size provides 81.8% power for a difference of 54 meters (the minimum clinically important difference) [96] in the 6-minute walk test (SD 135 based on our pilot data) and >99.9% power for a difference of 5.48 points (minimum clinically important difference) [97] for the Patient-Reported Outcomes Measurement Information System Physical Function score (SD 7.61 based on our pilot data). Assuming a correlation of 0.5 between significant results of step count and 6-minute walk test, the power of the study would be 80.7% (based on simulations) of having a statistically significant result for all 3 coprimary end points.

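### The Aim 2 durability rule requires neither a posttest benefit nor a remaining AB advantage at 6 months, so it can declare maintained benefit where there was none

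*Protocol article*

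**What the plan says.** The section on Aim 2 (Sustainability of AB) estimates persistence from "linear contrasts of the postintervention period to 6 months least-square means and analyzed as a noninferiority test of durability". The decision rule opens with "Noninferiority of AB in maintaining benefits relative to control will be declared if the lower 1-sided 95% confidence bound for a given coprimary outcome". The margin that this bound has to clear is the whole MCID of the outcome concerned, taken on the side that favours HEP. The contrast, the one-sided level and the margin are therefore all fixed in the article.

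The Power Analysis section uses the same MCIDs as the effects the trial is sized for: 1000 steps, 54 m on the 6-minute walk test and 5.48 points on PROMIS Physical Function. For step count, for example, the sample size is chosen "to detect the minimum clinically important difference in step count (1000 steps").

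The Aim 1 section defines trial success on the change from baseline to posttest for all three outcomes. The Aim 2 section does not make its test conditional on that result, outcome by outcome or overall. It sets no criterion for the AB-HEP difference at 6 months and gives no reason for the margin.

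**The concern.** The stated purpose of Aim 2 is to learn whether improvements last to 6 months. A contrast that starts at posttest carries no information about whether AB was ahead at posttest or is ahead at 6 months. If the arms never differ, the true contrast is zero, which is well inside the margin, and the rule will usually declare that AB maintained its benefits.

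The margin adds to this. It equals the whole benefit the trial was designed to detect. A benefit smaller than the MCID can therefore vanish completely while the true loss stays inside the margin.

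At stake is the durability claim, one of the trial's three aims. An outcome that failed at posttest, or whose advantage had gone by 6 months, could be reported as sustained.

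**Working it through.** **Inputs from the Power Analysis section.** MCIDs are 1000 steps, 54 m and 5.48 points. SDs are 2120, 135 and 7.61. There are 104 completers per arm, and the correlation between pre- and postintervention measures is 0.5.

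**Assumed, not in the article.** The posttest-to-6-month correlation r is taken as 0.5, with a range of 0.3 to 0.8.

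**1. Reproduce the plan's power.** SD of change = SD × √(2(1 − 0.5)) = SD. The SE of the between-arm difference in change is SD × √(2/104):
- steps: 2120 × 0.1387 = 294.0
- walk test: 135 × 0.1387 = 18.72 m
- PROMIS: 7.61 × 0.1387 = 1.055 points

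A two-sample noncentral t calculation at two-sided 5% gives 92.3%, 81.9% and 99.93%. The article states 92.3%, 81.8% and >99.9%, so the inputs are read as intended.

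**2. The Aim 2 rule.** Noninferiority is declared if estimate − 1.645 × SE > −MCID. For a true loss L relative to control, P(declare) = Φ((MCID − L)/SE − 1.645). MCID/SE is 3.401, 2.884 and 5.193.

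| Scenario (r = 0.5) | Steps | Walk test | PROMIS |
|---|---|---|---|
| Arms identical at every visit (L = 0) | 96% | 89% | >99.9% |
| Half-MCID benefit, all lost (L = MCID/2) | 52% | 42% | 83% |
| Full MCID lost (L = MCID) | 5% | 5% | 5% |

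Over r = 0.3 to 0.8, the first row runs 89% to >99.9%, 79% to 99.8%, and 99.7% to >99.9%. The second runs 42-85%, 34-74% and 71-99%.

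**3. Largest observed loss that passes**, MCID − 1.645 × SE:
- steps: 1000 − 483.6 = 516, or 52% of the MCID
- walk test: 54 − 30.8 = 23.2 m, or 43%
- PROMIS: 5.48 − 1.74 = 3.74 points, or 68%

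Over r = 0.3 to 0.8 the shares are 43-69%, 33-64% and 63-80%. They are shares of the benefit only when the posttest benefit equals the MCID.

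**4. Would 6-month superiority alone be better?** It needs an observed difference of about 1.96 × SE = 576 steps. From a 1500-step benefit it would tolerate a loss of about 1500 − 576 = 924 steps, where the plan's rule stops at 516. Superiority alone is therefore looser than the plan when the benefit is large.

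**5. Requiring both.** With all visit correlations at 0.5, the contrasts (6 months − posttest) and (6 months − baseline) have covariance 1 − 0.5 − 0.5 + 0.5 = 0.5 in units of the outcome variance, and variance 1 each. Their correlation is 0.5. If the full MCID is retained, both standardised means equal MCID/SE. The bivariate normal probability of exceeding 1.645 and 1.96 together is 90%, 77% and >99.9%. If there is no true difference at 6 months, the superiority part alone caps a false declaration at 2.5% per outcome.

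**The case against.** **The wording of Aim 2 presupposes a benefit.** It speaks of the persistence of a benefit, and Aim 1 will be reported beside it. With identical arms, Aim 1 would favour AB significantly only about 2.5% of the time per outcome. A true half-MCID benefit would reach significance at posttest only about 40%, 30% and 74% of the time, from Φ(MCID/(2·SE) − 1.96). So the rates above do not depend on the Aim 1 result, and a careful reader would see the failed primary result. That stands. But no condition is written, and the rule is applied to a given coprimary outcome. Trial success needs all three, so one outcome can fail at posttest and still be labelled durable. Nor is this detail left to a fuller document: the contrast, bound and margin are all stated, and as stated they do not support the claim.

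**An MCID margin is a recognised choice.** This stands too. It limits declaration to 5% when a full MCID is truly lost, so it does exclude a clinically important relative loss. A half-MCID margin at this sample size would have only 52% and 42% power for steps and walk test with zero true loss (r = 0.5).

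**A reader might infer that the rule generally lets AB lose half or more of its benefit.** The documents do not support that. The walk-test figure is 43%, all the shares assume a posttest benefit equal to the MCID, and they move with a correlation the article does not give. From a 1500-step benefit, 516 steps is 34%.

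**Conclusion.** The point holds for the rule as a whole, not for the margin on its own. Neither a posttest benefit nor a 6-month advantage is required, so the rule cannot support a claim that benefit was maintained. Arms that never differ would pass 96%, 89% and over 99.9% of the time, and a wholly lost half-MCID benefit would pass 52%, 42% and 83% of the time.

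These figures rest on the plan's SDs, simple change scores in 104 completers per arm, and the assumed correlation of 0.5. The planned mixed model could give a smaller SE, which would make the rule more permissive. The structural point, that identical arms have a true contrast of zero and sit inside the margin, depends on none of these values.

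A reader might also infer that the trial's efficacy conclusion is at risk. It is not: success is defined on baseline to posttest, and Aim 2 cannot alter it. This should be fixed for Aim 2.

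**What to change.** Restate the Aim 2 criterion. For each coprimary outcome that succeeded at posttest, declare durability only if both conditions hold:
- the existing noninferiority criterion on the posttest-to-6-month contrast is met; and
- the AB-HEP difference in change from baseline to 6 months, from the same shared-baseline model, favours AB at two-sided P<.05.

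Report the posttest-to-6-month contrast with its confidence interval in every case, so that readers can see how much benefit was lost. Add a sentence justifying the MCID as the margin.

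The cost is a change of wording in the analysis plan, made before unblinded data are seen. It needs no new participants, visits or models. The claim becomes harder: joint power is about 90% (steps), 77% (walk test) and over 99.9% (PROMIS) if the full MCID is retained, with all visit correlations assumed to be 0.5 and before the posttest condition is applied.

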##### Aim 3: Mediation and Moderation

We will explore the extent to which treatment-dependent effects are associated with a priori–defined mediators and moderators. Mediation analyses of postintervention change scores will be conducted following a causal model [98] that extends traditional models for mediation [99,100]. The magnitude of the mediated effect will be estimated as the natural indirect effect, which includes effects mediated by an interaction between the treatment and the mediator [101,102]. This extends the traditional Baron and Kenny method and is equivalent to the analysis of Kraemer et al [103] for the linear models. Tests of significance for natural indirect effect estimates will use 2-tailed *t* tests based on SEs estimated using the delta method. Mediation tests will be conducted separately for changes in outcomes of physical, emotional, and cognitive function and pain intensity. The possible effect of moderators of a beneficial effect of AB will be investigated by adding moderator (eg, gender and subjective vs objective cognitive decline), moderator × treatment, and moderator × treatment × visit interaction terms to the repeated-measures analysis of variance described for aim 1.

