#### Data Analyses

##### Overview

Our blinded statistician will conduct all data analyses using SAS (version 9.4) [92]. We will estimate treatment-dependent changes in primary (objective, performance-based, and patient-reported physical function) and secondary outcomes (patient-reported and objective cognitive function and emotional function). We will follow the intention-to-treat principle and include all randomized participants in our primary efficacy analyses. Data will be analyzed using a shared-baseline, linear mixed model with fully unstructured covariance among repeated measures. The shared-baseline assumption reflects the true state of the population before randomization and has the benefit of adjusting for chance differences at baseline. Linear mixed models with maximum likelihood estimation are unbiased when data are missing at random, conditional on the observed data. If loss to follow-up is strongly treatment-dependent (relative risk >2), we will use perturbed multiple imputation to assess the robustness of estimates from the primary model if data were missing in not-at-random manner.

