##### Aim 1: Efficacy of AB (Baseline to Posttest Period)

We have already established the feasibility benchmarks of the intervention and control [28,30]; therefore, emphasis of this study is on establishing the efficacy of AB*.* Accordingly, the primary analysis will compare the changes in primary and secondary outcomes (continuous measures) from baseline to posttest period between the randomized conditions. For each outcome, we will compare the effect of AB versus control on changes from baseline to the posttest period using linear contrasts. With 3 coprimary outcomes, no adjustment for multiple comparisons is needed; therefore, we will use 2-sided tests at *P*<.05 to declare the superiority of AB, maintaining an overall 5% type-1 error at our primary postintervention time point. The success of the trial will be declared if participation in AB is associated with statistically significant and clinically important improvement from baseline to posttest period over participation in control based on the 3 physical function outcomes.

We will conduct several sensitivity analyses to ensure that a conclusion about efficacy is robust to possible deviations from the assumptions of the primary model. Baseline parameters will be included to account for chance differences owing to randomization and to explain the sources of variation in response that are independent of treatment group. We will also use a Wilcoxon rank sum test comparing the change in scores between the 2 groups to avoid any parametric assumptions about the data. All secondary outcome measures will be analyzed using the same shared-baseline, linear mixed model and the same secondary sensitivity analyses. Step-down, Bonferroni-adjusted *P* values will be used to control for multiple comparisons regarding the secondary outcomes.

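### The Aim 3 moderation model omits moderator × visit and names no contrast, so testing the three-way term directly can report a prognostic effect as treatment moderation

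*Protocol article*

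**What the plan says.** The Aim 1 model is set out under Data Analyses, Overview: "Data will be analyzed using a shared-baseline, linear mixed model with fully unstructured covariance among repeated measures". Its rationale is that "The shared-baseline assumption reflects the true state of the population before randomization".

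Aim 3 (Mediation and Moderation) builds on that model and extends it for each moderator. Moderators will be examined by "adding moderator (eg, gender and subjective vs objective cognitive decline), moderator × treatment, and moderator × treatment × visit interaction terms".

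The list therefore has three entries: the moderator main effect, one two-way term with treatment, and the three-way term. Moderator × visit is not among them, and the Aim 1 text does not supply it. The nearest statement there is "Baseline parameters will be included to account for chance differences owing to randomization", which belongs to the sensitivity analyses and mentions no interaction with visit. Aim 3 does not say how treatment and moderator are coded, or which hypothesis is tested to declare moderation. It is introduced as exploratory.

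**The concern.** Moderation of benefit means that the AB-minus-HEP difference in change differs between moderator levels. A moderator may also be purely prognostic, with one level changing more than the other by the same amount in both arms. In a repeated-measures model that second effect belongs to moderator × visit. If this term is left out, the three-way term is the only place in the model where it can go, so a direct test of the three-way term mixes prognosis with moderation.

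ECD type is the stratification factor and a named moderator, and the Participants section gives testing moderation by ECD type as one reason for enrolling both types. The Discussion says the results will inform future trials. A spurious moderation result could therefore steer later work.

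A second, smaller point lies in the same list. Without restriction to post-baseline visits, moderator × treatment lets the arms differ at baseline within moderator levels, whereas the Overview adopts a model in which they share one baseline.

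**Working it through.** **Inputs from the protocol article.** 130 randomized and 104 completing per arm, step-count difference 1000, SD 2120, pre-post correlation 0.5, two-sided α 0.05 (Power Analysis); three visits (Assessments); SAS 9.4 and unstructured covariance (Overview).

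**Assumed, because the article gives no values.** Binary moderator with prevalence 30% or 50%; a shift g in change, in SD units, equal in both arms and at both post-baseline visits, from 0 to 0.5.

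**Anchor.** No operating characteristics are stated for moderation, so the stated step-count power is used to fix the setting. SD of change = 2120 × √(2(1 − 0.5)) = 2120. Standard error = 2120 × √(2/104) = 294. Noncentrality = 1000/294 = 3.40. The noncentral t distribution on 206 df gives 92.3%, as stated. The standardized effect is 1000/2120 = 0.47.

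**Algebra.** Let the mean change be:
- HEP: δ at moderator level 0, and δ + g at level 1
- AB: δ + τ at level 0, and δ + τ + g + m at level 1

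True moderation is [(δ + τ + g + m) − (δ + g)] − [(δ + τ) − δ] = m.

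Under the listed terms with 0/1 coding and HEP as reference, change in HEP is forced to be the same at both moderator levels. The three-way coefficient is then essentially the moderator difference in change within AB alone: (δ + τ + g + m) − (δ + τ) = g + m. With m = 0 it estimates roughly g instead of 0.

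**CLASS coding.** With visit, treatment and moderator as CLASS factors, the mean model has rank 8 without the three-way term and 12 with it (12 = 2 × 2 × 3 cells). The test carrying the three-way label has 12 − 8 = 4 df. Moderator × visit would use (2 − 1)(3 − 1) = 2 of these, so half of the tested space is pure prognosis.

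**Simulation.** 104 per arm, three visits, correlation 0.5, treatment effect 0.47 SD, no true moderation, unstructured GLS, 1000 replicates per row. The Monte Carlo standard error is about 0.7 points at 5% (√(0.05 × 0.95/1000)) and 1.4 points at 30%. Percentages are false rejection rates.

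| Prevalence | g (SD) | Listed terms, 0/1 coefficient | Mean estimate (SD) | 4-df omnibus | Moderator × visit added | Added, shared baseline kept |
|---|---|---|---|---|---|---|
| 30% | 0 | 4.6% | 0.00 | 5.0% | 6.0% | 6.5% |
| 30% | 0.2 | 13.9% | 0.19 | 18.0% | 4.3% | 4.3% |
| 30% | 0.3 | 26.2% | 0.29 | 40.7% | 5.5% | 4.7% |
| 30% | 0.5 | 55.8% | 0.47 | 86.7% | 4.3% | 4.6% |
| 50% | 0 | 6.2% | 0.00 | 5.1% | 5.0% | 5.5% |
| 50% | 0.2 | 16.7% | 0.18 | 21.5% | 5.3% | 5.1% |
| 50% | 0.3 | 32.0% | 0.28 | 50.5% | 5.8% | 6.6% |
| 50% | 0.5 | 62.6% | 0.45 | 93.1% | 4.8% | 3.7% |

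A separate run of 400 replicates gave 27–28% (coefficient) and 44–48% (omnibus) at g = 0.3.

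**When the error disappears.** With treatment coded ±0.5 and g = 0.5, the coefficient under the listed terms rejected in 4.2% (30% prevalence) and 5.8% (50%). The 4-df test is not rescued by coding (85.1% and 93.7%). An explicit difference-in-change contrast is safe under CLASS coding, because the rank is 12 with or without moderator × visit and the fitted cell means are therefore identical.

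**The case against.** The best defence is that the fitted model need not be wrong. Under ordinary CLASS coding the three-way term takes over the columns of the missing term, so the least-squares means are unchanged. The plan uses linear contrasts for Aims 1 and 2, and if Aim 3 is done the same way the answer is correct. This stands, and it limits the finding to direct tests of the three-way term. It does not remove the finding, because Aim 3 names neither a contrast nor a coding, so the protection is not written down.

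Next, nothing in the article shows that any moderator predicts change. On ECD type it leans the other way: the pilots saw no difference in outcomes by type (Participants), and the two types are described as presenting similarly (Discussion, Significance). This also stands. The shifts used above are assumptions, and at g = 0 every version is near 5%. Small pilots cannot exclude a prognostic difference, however, and the plan covers demographic and clinical moderators too.

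Third, a journal article condenses. Coding can fairly be left to a fuller plan, but the terms were not: the article lists them, including lower-order ones, and the list is incomplete as stated.

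Finally, relaxing the shared baseline costs some efficiency but does not itself bias the difference in change. That is accepted, and the baseline point is secondary.

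**Conclusion.** The point holds in a conditional form. If the three-way term is tested directly, as a 0/1-coded coefficient or as the CLASS omnibus test, and the moderator is prognostic for change, false moderation findings rise from about 5% to roughly 14–63% (coefficient) or 18–93% (omnibus) for assumed common shifts of 0.2 to 0.5 SD. These rates also rest on the assumed prevalences and on complete data for 104 per arm.

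Two stronger readings are tempting and are not supported. A reader might infer that the trial will report moderation by ECD type that does not exist. The article gives no evidence that ECD type predicts change, and it does not commit to the coefficient or omnibus test that would cause the error. A reader might also infer that the mediation test in the same section is faulty, since it uses t tests "based on SEs estimated using the delta method". That is a recognised and valid choice. In simulation with 208 participants and assumed mediator paths its type I error was 0% to 2.7%, so it is conservative, and lower power in an exploratory aim is not an error in the plan.

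The coprimary analyses, the success rule and the sample size are untouched.

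**What to change.** In Aim 3:
- Add moderator × visit to the listed terms.
- Enter treatment and moderator × treatment at post-baseline visits only, so that the shared baseline of the Aim 1 model is kept. The model is then visit, treatment × post-baseline visit, moderator, moderator × visit, and moderator × treatment × post-baseline visit.
- Name the moderation test: the difference between moderator levels in the AB-minus-HEP difference in change from baseline to posttest.

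The cost is a wording change, a few lines of code and one or two more parameters per moderator. No new data are needed, and the change can be made before the analyses, which the article schedules for completion by February 2027.

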## Results

The study was funded by the National Institute on Aging in December 2021. The study was approved by the IRB on December 8, 2021. We began recruitment in July 2022. As of March 2023, a total of 201 individuals have been referred and all have been contacted. Of these 201 individuals, we screened 141 (70.1%) and enrolled 37 (18.4%) participants (n=18, 49% in AB and n=19, 51% in HEP) across 4 group cohorts (largest group: n=10, 27%). All (37/37, 100%) participants completed the baseline assessment. Of the 37 participants, 1 (3%) dropped after the first AB session owing to an unrelated psychiatric hospitalization and 1 (3%) dropped after the second HEP session owing to extreme orofacial pain. In the three cohorts (26/37, 70%) that have completed the AB or HEP, 26 (100%) participants completed all 8 of the group sessions (including minimal makeups) and the posttest assessment. Adherence has been high for the Fitbit and ActiGraph watches, with 93.48% (1937/2072) valid days of wear compliance for both devices across the 2 group cohorts. The fourth group cohort is ongoing (9/37, 24%). We plan to complete enrollment by March 2026 and data analyses by February 2027.

